## Abstract

**Background:**

Sleep disorders are very common in the community and are estimated to affect up to 45% of the world’s population. Pharmacists are in a position to give advice and provide appropriate services to individuals who are unable to easily access medical care. The purpose of this study is to develop an intervention to improve the management of sleep disorders in the community. The aims are– (1) to evaluate the effectiveness of a community pharmacy-based intervention in managing sleep disorders, (2) to evaluate the role of actigraph as an objective measure in monitoring certain sleep disorders and (3) to evaluate the extended role of community pharmacists in managing sleep disorders. This intervention is developed to monitor individuals undergoing treatment and overcome the difficulties in validating self-reported feedback.

**Method/design:**

This is a community-based intervention, prospective, controlled trial, with one intervention group and one control group, comparing individuals receiving a structured intervention with those receiving usual care for sleep-related disorders at community pharmacies.

**Discussion:**

This study will demonstrate the utilisation and efficacy of community pharmacy-based intervention to manage sleep disorders in the community, and will assess the possibility of implementing this intervention into the community pharmacy workflow.

**Trial registration:**

Australian New Zealand Clinical Trial Registry: ACTRN12612000825853

## Background

Sleep disorders appear to be a global epidemic, affecting up to 45% of the world’s population [1]. Sleep disorders encompass problems with falling or staying asleep, waking up too early or too late, and problems with poor sleep quality, all of which may cause significant impairment of daytime functioning.

The community pharmacy is accessible and can provide services to patients who may not regularly come into contact with general practitioners or other traditional sources of health care [2]. Community pharmacy can therefore offer primary assistance for sleep-related disorders to the community. Even though specialist sleep clinics are available, they may not be accessible everywhere especially in rural and remote areas. These specialist clinics tend to focus very much on respiratory disorders of sleep and are considered as tertiary centres which treat later stage or more severe sleep disorders only. Community pharmacists are already in a suitable position to initiate conversation, discuss medicines, and provide ongoing follow-up [3] related to a range of health problems, and many interventions have been implemented for other chronic health problems such as asthma [4-8], diabetes [9-11] and hypertension [12,13]. There are many similarities between these chronic health problems and sleep disorders in terms of early intervention, community-level management and continuing care provision. This suggests that pharmacy-based management of sleep disorders could have a significant role in effectively reducing the burden of these disorders.

There are many types of sleep disorders, but by far the most prevalent in adults are insomnia and obstructive sleep apnoea (OSA) [14-16]. The current gold standard treatments for diagnosed OSA and insomnia patients are continuous positive airway pressure (CPAP) [17,18] and cognitive behavioural therapy (CBTi) respectively [19,20]. However, due to varying results or personal preference [21], many of these patients still present at the community pharmacy seeking additional or alternative treatment options [22,23]. Pharmacists also assist many ‘walk-in’ individuals who often use the community pharmacy as a primary contact to seek help for a variety of problems including sleep-related disorders. Many of these individuals have common or overlapping symptoms or simply present with ‘poor sleep’, thus make it difficult for health professionals to accurately assess and/or treat.

Currently, in managing sleep-related disorders, community pharmacists depend on self-report from patients or on sleep diaries, if indicated. Monitoring sleep disorders is difficult without appropriate tools, education or standard measures. Determining the actual sleep problem and planning meaningful strategies can therefore be complicated without objective measures. To date, in our knowledge, most studies involving sleep disorders in community pharmacies focused on screening tools [24-26] with very few studies incorporating patient follow-up and monitoring by community pharmacists [27].

This study will use a step-wise approach designed to tackle ‘poor sleep’ in all individuals with disturbed sleep, with referral procedures in place if the problem is not resolved. We will investigate the potential extended role of the pharmacists and the development of an intervention to monitor individuals with poor sleep using a convenient and portable measuring device as an objective measure to gain feedback on sleep. A wrist-actigraph (SBV2 Readiband™) allows pharmacy staff to follow those undergoing treatment by measuring the quality and quantity of sleep, and to better characterise their sleep. While monitoring treatment is difficult if self-reporting is poor, the use of actigraphy can overcomes this challenge by providing objective, patient friendly and graphical feedback that confirms certain sleep parameters and validates the self-reported feedback. An individual actigraphy report can be used as the focus reference in patients’ consultations regarding sleep.

As a portable device, the actigraph can record movement over extended periods of time, and has been used extensively in the studies of sleep and circadian rhythm [28-34]. Guidelines by the American Academy of Sleep Medicine (AASM) signified that actigraphy is a very useful method but it is not sufficient for all diagnoses. Clinical guidelines and research suggested that actigraphy is particularly useful in the evaluation of insomnia, circadian rhythm sleep disorders (e.g. advance sleep-phase syndrome (ASPS), delayed sleep-phase syndrome (DSPS), jet lag and shift work sleep disorder), sleep related breathing disorders (e.g. sleep apnoea), determination of response to treatment and in an evaluation of sleep patterns in special populations [28,29]. The actigraph can be used at home by patients without supervision from a trained sleep technician. Positive feedback was received in a feasibility study to determine the possibility and acceptability of actigraphy as a home-base sleep measure. Participants admitted no disruptions to daily tasks while wearing it [35].

This paper describes the research protocol of our study, developed as a community pharmacy-based intervention to improve the management of sleep disorders in the community.

### Research aims

The purpose of this study is to develop an intervention to improve the management of sleep disorders in the community. The aims are: (1) to evaluate the effectiveness of a community pharmacy-based intervention in managing sleep disorders, (2) to evaluate the role of actigraph as an objective measure in monitoring certain sleep disorders and (3) to evaluate the extended role of community pharmacists in managing sleep disorders.

## Methods and design

### Study design

This is a community-based intervention, prospective, controlled trial, with one intervention group and one control group (Figure 1).

**Figure 1 F1:**
[figure not shown]
Study design (File attached).

### Study setting

Four to five community pharmacies in the Brisbane metropolitan area with similar demographic criteria and physical locations will be recruited based on convenience sampling.

### Ethics approval

This project has been approved by the School of Pharmacy Ethics Committee, The University of Queensland (Reference number: 2012/04).

### Pharmacies

#### *Pharmacy eligibility criteria*

Community pharmacies that meet the following criteria are eligible to participate as a study site:

• Pharmacies that have high daily ‘walk-in customer’ turnover i.e. 100 to 300 customers per day for any ‘Pharmacist only medicine’, ‘Pharmacy medicine’, over-the-counter medicines including herbal supplements.

Additional criteria for the ‘Intervention care group’ pharmacies:

• Agree to install a software application (Sleep Consultant™ by Fatigue Science) which enables data to be downloaded from the actigraph to generate an individual sleep report for the participants.

• Have a private counselling area within the pharmacy where one-to-one consultations with customers will be separated from the common pharmacy counter.

• Able to follow-up participants for 2 weeks from baseline.

#### *Recruitment of pharmacies*

Contact information of the pharmacies will be obtained from the list of community pharmacies from publically available lists. Community pharmacies which meet the inclusion criteria will be invited to join the study by telephone and informed about the project. If the pharmacist expresses an interest, a research officer will arrange a face-to-face discussion for further explanation of the study and obtain consent. Upon agreement, the pharmacies will be assigned to either intervention or control group, based on convenience sampling.

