#### *Recruitment of participants*

Potential participants will be selected from walk-in customers who present at the participating pharmacies seeking help for sleep-related disorders or having symptoms of sleep problems. In both the intervention and control groups, in addition to the usual discussion and service about sleep health, the pharmacist or the pharmacy staff will invite potential participants to join the study. If they show an interest, further discussion will be provided at a private area in the pharmacy prior to obtaining consent. Those who agree to join the study, will be assigned to either intervention or control group participants, based on which pharmacy they attend.

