#### *Control participants - usual care group (UCG)*

The usual care group (UCG) participants will receive standard or usual care for sleep disorders based on the usual practice in the community pharmacy. Australian community pharmacies usually follow the Pharmaceutical Society of Australia’s recommended practice [45], which includes supplying ‘Pharmacy medicine’, ‘Pharmacist only medicine’, complementary medicine or other over-the-counter (OTC) medicines for sleep-related disorders, if indicated. At baseline, follow the same protocol as in the intervention group, study eligibility (Table 1) will be checked and inform consent will be obtained before the participants complete the ‘Initial Pharmacy Visit’ questionnaires. Baseline demographic and assessments will be completed for comparisons with the ICG participants. The UCG participants will be followed-up after two weeks by the study researcher via email or mail to complete the ‘End of Study’ questionnaires.

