#### *Study outcomes*

The primary outcomes (Table 2) of the study will be evaluated based on these three objectives:

1. To evaluate a community pharmacy-based ‘model of care’ to improve the management of sleep disorders in the community, by comparing:

a. Changes in HRQOL mean scores between and within the intervention care group (ICG) and usual care group (UCG) at baseline and week 2.

b. Changes in sleep scale mean scores – ESS, ISI, MAPI and IRLSSG, between and within the intervention care group (ICG) and usual care group (UCG) at baseline and week 2.

c. Changes in sleep parameter mean scores – sleep efficiency percentage (SE%), total sleep time (TST), number of nocturnal awakenings (NWAK) and sleep onset latency (SOL), between pre– and post–actigraphy sleep report data in the intervention care group (ICG).

2. To evaluate the role of actigraph as an objective sleep assessment instrument to monitor certain sleep disorders, by comparing:

a. Changes in sleep parameter mean scores –total sleep time (TST), number of nocturnal awakenings (NWAK) and sleep onset latency (SOL), between actigraphy and sleep diary at week 1 and week 2 in the intervention care group (ICG).

3. To evaluate the extended role of community pharmacists in managing sleep disorders in the community, by evaluating:

a. Participants’ opinions of sleep health at the end of the study.

b. Willingness and the amount able to pay if such programme is provided as a service in the community pharmacy.

Secondary outcomes (Table 2) to be evaluated are:

1. Participants’ opinions of the community pharmacy and opinions on the use of community pharmacy to seek help for sleep-related disorders.

2. Comparison between groups in sleep-related lifestyle and behaviours at week 2 follow-up.

3. Pharmacist and pharmacy staff opinions regarding the feasibility of the study and the management of sleep disorders in the community pharmacy after participating in the study.

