### Data analysis

Data will be collected from the sleep report generated from the Sleep Consultant™ software, sleep diary, and questionnaires (initial and end of study). Sleep parameters measurement, i.e. sleep efficiency percentage (SE%), total sleep time (TST), sleep onset latency (SOL) and number of nocturnal awakenings (NWAK) of a single participant through either the sleep diary or actigraphy will be averaged from all the data recorded during the 2-week period (recorded as ‘pre’ (week 1) and ‘post’ (week 2) mean scores). There will be no discrimination between weekdays and weekend data. Sleep scale scores to assess sleep health using ESS, ISI, MAPI and IRLSSG survey recorded at baseline and week 2 will be averaged to mean scores for analysis.

Data will be analysed using SPSS 20.0 for windows [53]. This study will consider alpha level of 0.05 for all statistical tests. Using descriptive, paired *t*-test and independent *t*-test – demographic characteristics and sleep scale scores between and within groups will be compared. In the ICG, pairwise differences of sleep parameters mean scores between actigraphy and sleep diary will be calculated using independent *t*-test, and will be used paired-*t*-test in comparing within group, for pre– and post–mean scores (for normally distributed data). To determine correlation between two variables, Pearson’s correlation will be applied. Likert-type questions will be analysed as descriptive analysis.

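### Between-arm questionnaire comparisons rest on convenience-assigned pharmacies and t-tests without covariates, so they are open to confounding and less precise than the collected baseline data allow

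*Protocol article*

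**What the plan says.** **Allocation.** Under Recruitment of pharmacies, once a pharmacy agrees, "the pharmacies will be assigned to either intervention or control group, based on convenience sampling". Under Recruitment of participants, customers who consent are placed in an arm "based on which pharmacy they attend". Nothing is randomised at either level.

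**Entry criteria.** One customer-turnover band applies to every pharmacy. Intervention pharmacies must also agree to install the actigraph software, be able to follow participants for two weeks, and "Have a private counselling area within the pharmacy where one-to-one consultations with customers will be separated from the common pharmacy counter".

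**Mitigation.** Study setting states: "Four to five community pharmacies in the Brisbane metropolitan area with similar demographic criteria and physical locations will be recruited based on convenience sampling".

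**Outcomes.** Study outcomes, item 1a, is "Changes in HRQOL mean scores between and within the intervention care group (ICG) and usual care group (UCG) at baseline and week 2". Item 1b says the same of ESS, ISI, MAPI and IRLSSG. Both are primary.

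**Baseline data.** Table 2 schedules WHO-5, the four sleep scales, demographics and lifestyle at T0 in both arms. For the control arm the text adds: "Baseline demographic and assessments will be completed for comparisons with the ICG participants".

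**Analysis.** Data analysis lists descriptive statistics, the paired t-test and the independent t-test, by which "demographic characteristics and sleep scale scores between and within groups will be compared". WHO-5 is not named in that sentence, and no other between-arm method is given for it. No baseline, demographic or pharmacy term appears. "This study will consider alpha level of 0.05 for all statistical tests".

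**The concern.** The two arms come from different pharmacies, placed by convenience and admitted under partly different criteria. Staff invite participants once the pharmacy's arm is fixed, and the offers differ: two weeks of actigraph, diary and two return visits in one arm, usual care and an emailed or mailed questionnaire in the other. Different people may accept. Baseline severity and other prognostic factors could then differ between arms for reasons unrelated to the intervention.

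Items 1a and 1b are the only between-arm score comparisons behind the aim of showing effectiveness, because actigraph and diary data exist in the intervention arm only. A t-test without covariates passes part of any baseline difference into the estimated effect. It also leaves unused the information that the baseline score carries about the week-2 score.

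This is not detail left to an analysis plan. The article names the tests, and the objection is to the choice it states.

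**Working it through.** **The plan's own figure.** Sample size gives 25 per group for a 20% difference between actigraphy and diary at 80% power and alpha 0.05. No SD is given, so the figure cannot be confirmed. Solved backwards for two independent groups (normal approximation, two-sided), 25 per group implies a standardised difference of 0.79, that is an SD of 20/0.79 = about 25% of the mean. The calculation does not concern intervention against usual care. It serves below only as the number per arm.

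**Inputs.**
- 25 per arm (Sample size); alpha 0.05, taken as two-sided.
- Correlation r between baseline and week-2 score: not in the documents, assumed 0.5 to 0.7.
- Baseline imbalance g in SD units: not in the documents. The illustration uses 0.4. The SE of a baseline difference with 25 per arm is √(2/25) = 0.28 SD, so 0.4 SD is 1.41 SE and would be exceeded in size about 16% of the time even under individual randomisation.

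**Bias when there is no true effect**, if both arms share the same regression of week-2 on baseline score:
- Raw week-2 comparison: r × g = 0.5 × 0.4 = 0.20 SD; 0.7 × 0.4 = 0.28 SD.
- Change-score comparison: −(1 − r) × g = −0.5 × 0.4 = −0.20 SD; −0.3 × 0.4 = −0.12 SD. The sign is opposite because the arm with the higher baseline regresses further.

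**Type I error at 25 per arm, nominal 5%:**

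| Imbalance | r | Raw week-2 | Change score |
|---|---|---|---|
| 0.3 SD | 0.5 | 8.3% | 8.3% |
| 0.3 SD | 0.7 | 11.5% | 7.0% |
| 0.5 SD | 0.5 | 14.3% | 14.3% |
| 0.5 SD | 0.7 | 23.6% | 10.5% |

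**Variance of the arm contrast**, relative to the raw week-2 comparison: change score 2(1 − r), ANCOVA 1 − r².
- r = 0.5: change 1.00, ANCOVA 0.75; ratio 0.75.
- r = 0.7: change 0.60, ANCOVA 0.51; ratio 0.51/0.60 = 0.85.

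The ratio of ANCOVA to change score is (1 + r)/2, below 1 for any r below 1.

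**What that buys at 25 per arm.** The detectable difference at 80% power is 2.80 × √(2/25 × variance factor).

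| r | Quantity | Raw week-2 | Change score | ANCOVA |
|---|---|---|---|---|
| 0.5 | Detectable difference (SD) | 0.79 | 0.79 | 0.69 |
| 0.5 | Power for an assumed 0.5 SD effect | 42% | 42% | 53% |
| 0.7 | Detectable difference (SD) | 0.79 | 0.61 | 0.57 |
| 0.7 | Power for an assumed 0.5 SD effect | 42% | 63% | 70% |

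**Limits of these figures.** They treat participants as independent and ignore clustering by pharmacy. An actual baseline imbalance costs ANCOVA a little: at 0.4 SD it adds about 0.4²/48 = 0.0033 to 2/25 = 0.08, or 4% of the variance.

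**The case against.** **Baseline already enters the outcome.** A reader might infer that baseline scores serve only to describe the groups. Study outcomes does not support that: it defines items 1a and 1b as changes. If the independent t-test is run on change scores, part of a baseline difference is removed, and the raw week-2 bias is not the relevant figure. This stands, which is why both biases are shown. Data analysis does not say which score is tested, and either choice leaves a bias under the stated model and a larger variance than ANCOVA.

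**The sites are meant to be alike.** A reader might infer that the arms are in fact confounded, or that control pharmacies have no private space. The documents show neither. Sites are chosen for similar demographics and location, one turnover band applies to all, and Recruitment of participants places the pre-consent discussion in a private part of the pharmacy in both arms. The follow-up and software criteria largely reflect intervention workflow. This too stands. But similar location and turnover do not settle which customers accept each offer, or which pharmacy was convenient for which arm.

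**ANCOVA is not automatically right for pre-existing groups.** If each arm regresses to its own stable mean, the change score is unbiased and ANCOVA is not. This is fair. The case for ANCOVA is better precision and removal of measured imbalance under its model, not proof of a causal effect.

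**The design is openly non-randomised and pragmatic.** The article calls the trial controlled, not randomised. That is honest labelling, but it strengthens the case for adjustment. The Discussion in the abstract still promises that the study will demonstrate efficacy.

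**Conclusion.** The concern holds in this form: the between-arm contrast on WHO-5 and the sleep scales is open to confounding of unknown size and direction, and is less precise than it need be. The bias and variance figures are illustrations that depend on the assumed imbalance, on r, and on a common regression in both arms; they do not predict what this trial will show.

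Two stronger inferences are not supported. Adjustment cannot turn this into a randomised comparison: with 4 to 5 pharmacies nested in arm, a fixed pharmacy effect cannot be separated from the arm effect, and a pharmacy-level analysis has only 2 to 3 degrees of freedom. Nor does the point reach the actigraph and diary outcomes, which have no T0 value and no control arm.

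**What to change.** **Analysis (wording only).** In Data analysis, replace the between-arm independent t-test for WHO-5 and the sleep scales with a regression of the week-2 score on arm, baseline score and a short prespecified list of covariates already collected, for example age and sex. Report the adjusted difference with its confidence interval. No new data are needed.

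**Interpretation (wording only).** State that the comparison is non-randomised and that adjustment cannot remove pharmacy-level confounding with 4 to 5 pharmacies. Temper the claim of demonstrated efficacy to match.

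**Allocation, if pharmacies are not yet assigned.** Apply the same entry criteria to every candidate pharmacy, obtain consent, and then draw the arms at random. The cost is a slightly smaller pool of eligible pharmacies, with no added visits or participants. With so few sites a draw does not guarantee balance, and staff would still invite participants knowing the arm, so the analysis change is needed either way.

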#### *Training for pharmacists and pharmacy assistants*

This study will involve both pharmacists and pharmacy assistants. One survey found that only 30% of direct sleep product requests were handled entirely by pharmacists and in a symptom based scenario, only 18% of requests were handled by pharmacists [36]. Thus pharmacy assistants will be included to reflect common practice and support the pharmacists.

Pharmacists and pharmacy assistants from the intervention pharmacies will attend a half-day training course provided by a sleep psychologist focusing on the use of the actigraph and sleep diaries, sleep scale scores assessment and questionnaires, and provide information on a healthy lifestyle and sleep-related disorders. The actigraph user’s manual will be provided.

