**Eligibility criteria**	
**Inclusion**	**Exclusion**
• Aged ≥ 18 years old	• Aged < 18 years old
• Attend a participating pharmacy as a ‘walk-in customer’ seeking help for sleep-related disorders or having symptoms of sleep disorders.	• Not able to speak, read and write in English, or not fluent in English and cannot arrange for a translator themselves or a translator is not available.
	• Unable to complete the screening (in the pharmacist’s opinion).
	• Refuse to give consent.
	• Pregnant.
	• Currently under treatment with continuous positive airway pressure (CPAP)

The actigraph is a useful device for monitoring sleep-related disorders, but literature suggests that it should be used in conjunction with other parameters, such as sleep diaries [31,42] as both may complement each other by providing objective and subjective data, respectively. Therefore, participants will be provided with an intervention package, which includes:

1. An actigraph (SBV2 Readiband™) to be worn 24-hours a day for seven days before participants revisit the pharmacy for their first follow-up, and then for a further seven days after the first follow-up before returning to the pharmacy for final assessment.

2. A sleep diary [43] to self-record 14 days of bedtime, wake time, time to fall asleep, number of nocturnal awakenings and total sleep time, plus information related to sleep-hygiene, lifestyle and other factors that may interrupt sleep.

3. Educational information about sleep disorders, sleep health management, sleep hygiene and healthy lifestyle to improve sleep (via access link to a website: http://sleepproblemandyou.wordpress.com/ which is developed specifically for this study). The web address will be provided to each participants.

One complete study duration for a participant in the intervention group is two weeks with follow-ups at two time points; week 1 (day 8) and week 2 (day 15). At both time points, pharmacy staff will analyse the data downloaded from the actigraph using Sleep Consultant™ software to generate an on-the-spot individualise report of sleep/wake patterns and they will also assess the self-report information from the sleep diary.

##### 

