### Study measurements and outcomes

#### *Study measurements*

Assessments will be conducted at three times points – baseline, week 1 and week 2 (Table 2). At baseline upon recruitment, participants will be assisted to complete the self-administered ‘Initial Pharmacy Visit’ questionnaires, comprise of:

• Demographic and lifestyle information, which includes sleep environment, smoking, alcohol consumption and caffeinated drinks intake, modified from the validated ‘Pharmacy Tool for Assessment of Sleep Health - POTASH’ [24].

• Health-related quality of life (HRQOL) assessment using validated WHO-Five Well Being Index (version 1998) [46,47].

• Sleep health assessment using a set of survey instruments adapted from POTASH [24]: Epworth Sleepiness Scale (ESS) [48,49], Insomnia Severity Index (ISI) [50], Multivariate Apnea Prediction Index (MAPI) [51] and International Restless Legs Syndrome Study Group (IRLSSG) [52].

• Community pharmacy survey: 14 questions using a 5-point Likert-type scale from 1 (strongly disagree) to 5 (strongly agree), and one open ended question.

**Table 2 T2:** Summary of measurements and study outcomes

**Measurements**	**Instruments**	**Group**	**T0**	**T1**	**T2**	**Outcome**	
Surveys/measuring tools							
Socio-demographic and lifestyle	Questionnaire	ICG, UCG	x				2˚
Health-related quality of life ^I,E^	WHO-5 Well-being index (1998)	ICG, UCG	x		x	1˚	
Sleep scale scores ^I,E^	ESS, ISI, MAPI, IRLSSG	ICG, UCG	x		x	1˚	
Community pharmacy survey ^I^	Questionnaire	ICG, UCG	x				2˚
Close-out survey ^E^	Questionnaire	ICG, UCG			x	1˚	2˚
Sleep parameters assessment							
SE%	Actigraph only	ICG		x	x	1˚	
TST, NWAK, SOL	Actigraph and sleep	ICG		x	x	1˚	
	diary						
Other factors that may interrupt sleep	Sleep diary only	ICG		x	x	1˚	
Pharmacy survey							
Close-out survey for pharmacy	Questionnaire	Pharmacists, pharmacy staff			x		2˚

T0 = baseline, T1 = 1 week after baseline, T2 = 2 weeks after baseline.

ICG: intervention care group; UCG: usual care group.

ESS: Epworth Sleepiness Scale; ISI: Insomnia Severity Index; MAPI: Multivariate Apnea Prediction Index; IRLSSG: International Restless Legs Syndrome Study Group.

SE%: Percentage of sleep efficiency; TST: Total sleep time per-24 hour period; NWAK: Number of nocturnal awakenings; SOL: Sleep onset latency.

1˚: Primary outcome; 2˚: Secondary outcome.

I: ‘Initial Pharmacy Visit’ Questionnaires; E: ‘End of Study’ Questionnaires.

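### Training on shared recruitment and baseline procedures is described for intervention pharmacies only, so recruitment, and possibly help with the baseline scales, can differ by arm

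*Protocol article*

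**What the plan says.** - **Training.** Under Training for pharmacists and pharmacy assistants, "Pharmacists and pharmacy assistants from the intervention pharmacies will attend a half-day training course provided by a sleep psychologist". Besides the actigraph and diary, the content includes "sleep scale scores assessment and questionnaires, and provide information on a healthy lifestyle and sleep-related disorders". No training is described for control pharmacies.
- **Recruitment.** For both groups, "the pharmacist or the pharmacy staff will invite potential participants to join the study" (Recruitment of participants).
- **Allocation.** Under Recruitment of pharmacies, "the pharmacies will be assigned to either intervention or control group, based on convenience sampling". Participants then "will be assigned to either intervention or control group participants, based on which pharmacy they attend", so the arm is known before anyone is approached.
- **Entry criterion.** Table 1 admits adult walk-in customers "seeking help for sleep-related disorders or having symptoms of sleep disorders". It sets no scale threshold, and one exclusion (inability to complete screening) is left to the pharmacist's judgement.
- **Baseline.** For the usual care group, "At baseline, follow the same protocol as in the intervention group, study eligibility (Table 1) will be checked". Under Study measurements, "participants will be assisted to complete the self-administered ‘Initial Pharmacy Visit’ questionnaires". Neither sentence names the person who helps.
- **Use of the baseline scores.** Primary outcomes 1a and 1b are changes from baseline to week 2 in WHO-5, ESS, ISI, MAPI and IRLSSG, between and within groups. Data analysis names t-tests at an alpha of 0.05 for the scale scores and no baseline-adjusted comparison.

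**The concern.** Training on the actigraph, the diary and sleep advice is part of the intervention and belongs in one arm. Recognising an eligible customer and handling the baseline questionnaires are trial procedures common to both arms, yet the course that covers them is described for one arm only.

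Staff who have just been taught about sleep disorders may notice and invite a different mix of customers from staff who have not. They may also help differently with the scales. Either would make the groups differ at baseline for a reason unrelated to the treatment effect, and the between-group primary outcomes start from that baseline.

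**Working it through.** The article gives no figure on this point to reproduce. The check has two parts.

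**1. The sections side by side**

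| Step | Intervention pharmacies | Control pharmacies |
|---|---|---|
| Training on scales, questionnaires, sleep disorders | Half-day course | None described |
| Finding and inviting customers | Pharmacy staff | Pharmacy staff |
| Eligibility | Table 1 | Table 1, same protocol |
| Baseline scales | Self-administered with help; helper not named | Same protocol; helper not named |
| Week-2 scales | At the pharmacy visit | By email or mail from the researcher |

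The recruitment difference follows from the text. The difference in help with the scales is an inference.

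**2. Size, by illustration**

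Inputs from the article: n = 25 per group, two-sided alpha 0.05. Assumptions: no true effect, equal SDs, normal approximation, no clustering, a baseline shift of d SD between arms, and a baseline to week-2 correlation r of 0.5 to 0.8.

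The standard error of a difference in means is √(2/25) = 0.283 SD. For a standardised bias e, the rejection probability is Φ(e/0.283 − 1.96) + Φ(−e/0.283 − 1.96).

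*(a) Case finding.* If the arms are selected to differ by d at baseline and regress towards a common mean, the week-2 difference is r·d. The difference in change is (1 − r)·d, and the SD of change is √(2(1 − r)). Hence e = (1 − r)·d / √(2(1 − r)).

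| d (SD of score) | r = 0.5 | r = 0.7 | r = 0.8 |
|---|---|---|---|
| 0.2 | e = 0.100, 6.4% | e = 0.077, 5.9% | e = 0.063, 5.6% |
| 0.3 | e = 0.150, 8.3% | e = 0.116, 7.0% | e = 0.095, 6.3% |
| 0.5 | e = 0.250, 14.3% | e = 0.194, 10.5% | e = 0.158, 8.6% |

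*(b) A shift at baseline that is wholly absent at week 2*, as when help changes the baseline answers only. The whole shift enters the change, so e is the shift in SD of change.

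| Shift (SD of change) | e/0.283 | Rejection |
|---|---|---|
| 0.1 | 0.354 | 6.4% |
| 0.2 | 0.707 | 10.9% |
| 0.3 | 1.061 | 18.6% |

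The units of (a) and (b) coincide at r = 0.5, where √(2 × 0.5) = 1. At r = 0.8 the SD of change is √0.4 = 0.632 SD of score.

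**The case against.** **The scales are self-administered.** The sentences on control baseline are passive, and the only person named for control data collection is the researcher at week 2. A reader might infer that untrained control staff score the scales differently. The article does not say that, so this limb stands only as a possibility.

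**Control staff may be briefed.** A research officer meets interested pharmacists face to face, and a condensed article may leave a routine site briefing to the full protocol. The absence of a described control briefing is therefore no finding in itself, and a reader should not infer that control staff get no instruction. What stands is that the article places shared content in a course confined to one arm.

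**Staff behaviour is not documented.** Many customers will present themselves for help, and the same Table 1 applies in both arms. No section shows that trained staff will recruit milder cases. If they did, there would be less room for improvement in the intervention arm, which could work against the intervention. The direction is therefore unknown.

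**A severity difference largely cancels in a change score.** This is right. A reader might infer that any baseline shift passes whole into the between-group difference, giving 11 to 19%. For case finding that is not so, because only the part due to regression to the mean remains. The larger figures need a shift confined to baseline. That is not far-fetched, because control participants answer at week 2 by email or mail and any help in the pharmacy need not recur, but the article does not establish it.

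**Training is not the main source of selection.** Convenience allocation and arm-aware recruitment would leave the groups open to differ even with identical training. This also stands.

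**Conclusion.** The concern holds in a limited form. As described, the plan lets recruitment differ by arm, because training in shared procedures is set out for one arm while staff in both arms apply an open, partly judgement-based criterion knowing the arm. Differential help with the baseline scales is possible but not shown.

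For case finding, the false-positive rate of one between-group comparison of change rises from 5% to about 6% at a 0.2 SD shift and about 6 to 8% at 0.3 SD. It reaches 11 to 19% only if a shift of 0.2 to 0.3 SD of change is present at baseline and gone by week 2. The shifts and the correlation are assumptions; the article gives neither. The inflation is modest in the better-supported case, but the remedy is cheap and has to be in place before recruitment starts.

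**What to change.** 1. Split the training. Give staff in both arms the same short scripted module on whom to invite, how to apply Table 1, and how to help with each scale without interpreting it. Keep the actigraph, diary-interpretation and sleep-advice training for the intervention arm.
2. State who helps with and who scores the baseline questionnaires in each arm.
3. Log customers approached, eligible and consented, by arm, so that differential recruitment can be seen.
4. Adjust the between-group comparison for baseline score. This deals with measured severity only. It does not remove selection on unmeasured factors or repair a baseline collected differently in the two arms.

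**Cost.** One short briefing at each control pharmacy and a simple log. The study plans four to five pharmacies in total (the split is not stated), and the research officer already meets interested pharmacists in person. The downside is slightly greater awareness of sleep problems among control staff, which leaving out all management content keeps small. Bias from non-random, arm-aware recruitment would remain and should be acknowledged as a limitation.
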